## Abstract

**Background:**

About 50% of women experience lumbopelvic pain (LBPP) during their pregnancy. LBPP has negative repercussions on sleep, social and sexual life, physical and work capacity, and psychological health and contributes to physical inactivity. The benefits of LBPP prevention or treatment in pregnant women through specific exercises should therefore be further investigated. This study protocol has been designed to establish the feasibility of implementing motor control exercise program with pregnant women presenting with a history of LBPP.

**Methods/design:**

Forty pregnant women with a history of LBPP will be recruited and randomly allocated to a control (20 participants) or intervention (20 participants) group. The control group will receive standard prenatal care, including basic information on what to do when suffering from LBPP. The intervention group will participate in three 40-min exercise sessions per week from < 20 weeks until 34–36 weeks of gestation: one supervised group session via the Zoom platform (once a month, this session will take place at the *Université du Québec à Trois-Rivières*) and two unsupervised sessions at home. A motor control exercise program will be developed to target strengthening of the lumbo-pelvic-hip core muscles and improve spinal and pelvic stabilization. Participants of this group will also receive standard prenatal care. Women of the control group will receive after 6 weeks postpartum an exercise program designed to reduce LBPP they may have developed during pregnancy and that may persist after delivery. Primary outcomes will be participants’ recruitment, retention and adherence rates, safety, and acceptability of the intervention. Secondary outcomes will include LBPP incidence, frequency, and intensity, as well as self-reported functional disability, physical activity levels, fear avoidance behavior, anxiety, and depression.

**Discussion:**

This study will inform the feasibility of conducting a full-scale randomized controlled study to test the effectiveness of a motor control exercise program on the prevention and treatment of LBPP in women with a history of LBPP. Adequate prevention and treatment of pregnant women with a history of LBPP should help limit the recurrences of LBPP or the aggravation of its intensity during pregnancy.

**Trial registration:**

US National Institutes of Health Clinical Trials registry NCT04253717 April 27, 2021.

**Supplementary Information:**

The online version contains supplementary material available at 10.1186/s40814-022-01024-0.

## Background

Approximately 50% of women experience low back pain (LBP) or pelvic girdle pain (PGP) during pregnancy, and 25% will still experience pain one year after delivery [1]. A 10-year follow-up study reported that 1 in 10 women who had PGP during pregnancy still has severe consequences up to 11 years after delivery [1–5]. LBP is defined as pain or discomfort located between the 12th rib and the gluteal fold, whereas PGP has been defined as “pain experienced between the posterior iliac crest and the gluteal fold” [6]. When pregnant women have both types of pain (i.e., LBP and PGP), the pain is commonly referred to as lumbopelvic pain (LBPP). Indeed, there seems to be a consensus (despite variation in definition) that the term LBPP is used when no distinction is made between LBP and PGP [5].

Several hypotheses have been suggested to explain the development of LBPP during pregnancy. Hormonal, anatomical, biomechanical, and postural changes likely interact in the development of pregnancy-related LBPP [6–8]. As the fetus grows, the women’s center of gravity moves towards the abdomen. This results in an increased lumbar lordosis, posterior tilt of the sacrum, and consequent backward extension of the head relative to the back to compensate for the increased lumbar lordosis and weight [9–11]. Moreover, the increased lumbar lordosis is believed to not only change the load distribution between the different structures of the spine, but also to increase the facet joint load sharing contribution, which would contribute to LBPP [12]. Accordingly, a study published in 2003 reported that pregnant women with LBPP suffered more from postural constraints, such as a forward shifting of the trunk center of mass, than pregnant women without LBPP [13]. Inefficient neuromuscular control is believed to contribute to the etiology of LBPP in pregnant women [6]. One study investigated LBPP intensity and disability in pregnant women with and without LBPP before pregnancy [14] and found a significant correlation between current pain intensity and lumbar muscles activity level during trunk flexion. The study also reported that paraspinal muscles activity during bending measured in the first trimester of pregnancy was significantly correlated with pain intensity measured in the third trimester [14].

One important risk factor for developing LBPP during pregnancy is having a history of LBPP [15]. Furthermore, early LBP in pregnancy appears to be a predictor for long-term PGP [2]. Interestingly, a comprehensive review reported that the mean prevalence of postpartum LBPP was higher in studies of pregnant women with a history of LBP (42.7%) compared to when they were excluded from studies (24.3%) [5]. It is therefore of paramount importance to gain knowledge on these women because the literature shows that pregnant women with a history of LBPP have a threefold increased risk to develop LBPP during their pregnancy compared to pregnant women without a history of LBPP [5].

Despite its high prevalence, LBPP during pregnancy is often considered a common and almost natural phenomenon which often leads to inadequate clinical prevention and treatment of the condition [16]. LBPP has negative repercussions on sleep, social and sexual life, physical and work capacity, as well as on psychological health [17, 18]. Importantly, LBPP also contributes to physical inactivity during pregnancy [19], which has been associated to a higher incidence of maternal and neonatal complications [20–23]. Despite the frequent occurrence of LBPP during pregnancy and the significant impact it can have on the women’s quality of life, there are currently no specific guidelines available to inform clinical prevention and treatment of this condition. Not surprisingly, several studies indicate that about 25 to 30% of women suffering from LBPP self-manage or seek a wide range of interventions delivered by various care providers to prevent and treat their symptoms [24, 25]. However, the evidence regarding these interventions is limited due to restricted availability of high-quality studies and very low evidence strength [26, 27]. It is therefore essential to identify effective clinical strategies to prevent and treat pain and disability, while considering the safety of both the mother and growing fetus.

The recently published *2019 Canadian guideline for physical activity throughout pregnancy* [20] clearly highlights that, not only is exercise safe for both the mother and the growing fetus, but that it also improves key pregnancy outcomes such as decreased risk of gestational hypertension and diabetes [22], excessive gestational weight gain [23] and depression [28]. The guideline summarizes the best available evidence and provides consensus-based recommendations on physical activity during pregnancy. It suggests that women without any medical restriction should accumulate at least 150 min of a variety of moderate-intensity physical activity each week to achieve clinically meaningful reduction in pregnancy complications, such as gestational diabetes mellitus, gestational hypertensive disorders, and prenatal depression [21]. Nonetheless, the guideline does not provide any specific recommendation for the prevention and treatment of LBPP during pregnancy, mainly due to the lack of evidence regarding the effect of prenatal exercise on the occurrence of pregnancy-related LBPP and the poor quality of evidence (i.e., “very low”) and heterogeneity of the data regarding its effect on LBPP intensity [22]. Considering that a history of LBPP is one of the strongest predictors of LBPP during pregnancy [15] and that it is a debilitating condition associated with significant personal, social, and economic burden [17, 18, 29], exercise may offer a safe and cost-effective self-management strategy option to decrease the recurrences and symptom intensity of LBPP for expecting mothers with a history of LBPP. However, more robust research is needed to identify suitable or effective exercise modalities to optimize self-management of LBPP in these women.

The primary objective of the study described in this protocol is to assess the feasibility of implementing a motor control exercise program with pregnant women presenting a history of LBPP in order to reduce LBPP recurrences or limit its intensity. The secondary objective is to assess the potential effectiveness of the program. The first hypothesis is that the motor control exercise program will show high recruitment, adherence rates as well as low attrition among pregnant women with a history of LBPP in the intervention group. The second hypothesis is that the proposed motor control exercise program will reduce LBPP recurrences or limit its intensity.

## Methods/design

### Design

This study is a parallel randomized controlled feasibility trial involving two groups of pregnant women with either a history of LBPP or current LBPP. Participants are randomized to either standard prenatal care or standard prenatal care combined with a motor control exercise program (allocation ratio 1:1). It has been designed to assess the feasibility and the potential effectiveness of a motor control exercise program to reduce LBPP recurrences or limit its intensity in pregnant women with a history of LBPP. This study protocol complies with the guidelines of the SPIRIT checklist [30]. The proposed study protocol has been approved by the institutional review boards of the *Université du Québec à Trois-Rivières* (CER-19-259-07.20) and *Centre Intégré Universitaire de Santé et de Services Sociaux de la Mauricie-et-du-Centre-du-Québec* (CIUSSS-MCQ, local health services) (CÉRM-2019-004-01). The study will take place at the *Université du Québec à Trois-Rivières* and has been registered at Clinicaltrials.gov (NCT04253717). Before any intervention be initiated, participants will provide written informed consent in accordance with the certification delivered by the institutional review boards.

### Recruitment

Recruitment of participants will be conducted at local medical clinics as well as in the local community via social media including Facebook. Medical teams will talk to pregnant women about the study and, if they are interested in participating, a research team member will meet with them and provide an overview of the study purpose and content. Those willing to participate in the study will be met at the university laboratory for the pre-intervention visit. At this visit, informed written consent will be obtained, and baseline demographics and physical measures will be collected. Participants will also complete questionnaires assessing functional disability, physical activity levels, fear avoidance behavior, anxiety, and depression. At the end of the pre-intervention visit, a member of the research team will open a sealed opaque envelope in front of the participant to reveal the participant’s random allocation to one of the two groups (intervention or control group).

### Eligibility criteria

Pregnant women aged 18–40 years old, carrying one fetus and being ≤ 20 weeks pregnant (based on the ultrasound performed in the first trimester of pregnancy) and presenting with a history of LBPP (currently in pain or not) will be eligible to participate in the study. Women undergoing their first LBPP episode (of at least 2 weeks duration) will also be included. The inclusion criteria are based on the potential full-scale trial objective to reduce LBPP recurrences or limit its intensity in pregnant women with a history of LBPP. To confirm the presence and intensity of LBPP and women’s eligibility for the trial, a medical history and recommended clinical tests [6, 31] will be conducted at the pre-intervention visit (baseline) by a member of the research team. Women presenting any of the following conditions will be excluded from the study: inflammatory rheumatic disease, infectious disease, neuromuscular disease, vascular disease, connective tissue disease, severe disabling pain, and neurologic signs and symptoms. Women presenting contraindications to exercise (according to the 2019 Canadian guideline for physical activity throughout pregnancy [21]) will also be excluded from the study. Women unable to understand or speak French as well as those unwilling to be randomized will also be excluded.

### Sample size

Pregnant women will be recruited and randomly allocated to a control (20 participants) or intervention (20 participants) group. A sample size of 40 pregnant women was chosen based on a previous study we conducted and in which we were able to recruit 40 pregnant women in twelve months [32] and considering that over 4600 women gave birth at the local health services in 2016–2017 (including 1800 at the *CIUSSS-MCQ*) [33]. Furthermore, one of the study goals is to obtain an estimate of variance for the primary outcomes of a full-scale study. A minimally clinical important difference between groups has already been established and it is suggested that 10 to 20 participants per group is sufficient to inform feasibility and to plan for a larger study [34]. Between group differences in LBPP and disability score after the intervention will be used to estimate adequate sample size for future research planning.

### Randomization

At the end of the pre-intervention visit, participants will be randomly allocated to one of the two groups. The randomization sequence generation will be performed by an independent research assistant using a computer random number generator while the allocation sequence concealment will be performed using sequentially numbered, opaque and sealed envelopes. To ensure good balance of factors known to affect the natural history of pregnancy-related LBPP in our small sample, two minimization criteria will be considered: baseline pain intensity and baseline physical activity levels. Participants will not be blinded to intervention allocation, but the content of the exercise sessions will be shared only to those randomized to the intervention group to prevent cross-contamination between groups. The kinesiologist who will prescribe and supervise the exercise sessions will not take part in the pre- and post-intervention evaluations. The member who is running the pre- and post-intervention evaluations and who is managing the database, as well as the person who is supervising the exercise sessions, are not blinded. Members of the research team involved in statistical analyses will be blinded to group allocation.

### Intervention

#### Control group

Pregnant women in the control group will receive standard prenatal care, including basic information on what to do when suffering from LBPP, which is provided in the practical guide *From Tiny Tot to Toddler*
*[*35*]**. *This guide, published by the *Institut National de Santé Publique du Québec*, is offered at no cost to all pregnant women in the Province of Quebec [35]*.* After 6 weeks postpartum, women will receive an exercise program designed to reduce LBPP they may have developed during pregnancy and that may persist after delivery.

#### Intervention group

Pregnant women in the intervention group will participate in three 40-min exercise sessions per week from ≤ 20 weeks of gestation until 34–36 weeks of gestation: one supervised group session via the Zoom platform (once a month, this session will take place at the *Université du Québec à Trois-Rivières*) and two unsupervised sessions at home.

All sessions will include a 5-min warm-up period followed by specific exercises of moderate-intensity aimed at strengthening muscles of the lumbo-pelvic-hip core complex in order to improve stabilization and alignment of the spine and pelvis (transversus abdominis, internal obliques, multifidus, pelvic floor, thigh, and hip muscles) [36, 37]. The sessions will end with gentle stretching. No specific equipment will be needed to complete the home exercise component of the program. The intervention will be adapted to the stage of pregnancy and related discomfort to ensure a safe, individualized, and yet motivating training experience for each participant. Women will receive a weekly text message with an individually tailored home-exercise program to be completed before the next group session. The text message will contain a link giving access not only to the weekly exercise program, but also to a web-based electronic diary to help participants document their participation in the home exercise sessions (compliance and adverse events), incidence (a painful episode), frequency, and intensity of daily LBPP, as well as any treatment received to prevent and treat LBPP. Participants of this group will also access the same standard prenatal care recommendations as the control group, which includes basic information about what to do when suffering from LBPP, which is provided in the practical guide“ *From Tiny Tot to Toddler”* [35]*.*

### Data collection

#### Primary outcome measures

##### Feasibility components: recruitment, retention, adherence rate, safety of the intervention, and acceptability

The feasibility of recruitment, evaluated for both groups at the pre-intervention visit, will be defined as the ability to recruit eligible women throughout a 12-month period. The feasibility of obtaining a successful retention rate and consequently low attrition will be assessed using the completion of pre- and post-intervention questionnaires (see below). Adherence to the protocol will be defined as attendance to the supervised group exercise sessions and completion of the unsupervised home exercise sessions. The retention and adherence rates will be evaluated for the intervention group at the post-intervention visit. Safety of the intervention will be determined based on the number of adverse events, which will be defined as symptom flare-ups that will prevent a woman from taking part in subsequent exercise sessions or injuries requiring medical attention. In addition to the kinesiologist taking note of any undesirable effects during supervised exercise group sessions, women from the intervention group will be asked to report, via weekly text messages and their web-based diary, any reaction or flare-up that is not consistent with their usual pain presentation as a result of either home exercise or supervised group exercise sessions. Information concerning adverse events will be collected for the intervention group on a weekly basis throughout the study. Acceptability of the intervention, assessed for the intervention group at the post-intervention visit, will be determined based on how the intervention will be perceived by pregnant women (including satisfaction, practicality and accessibility assessed using 5-point Likert scales).

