***Secondary outcomes measures***				
***LBPP incidence, frequency and intensity***		X	X	X
***Functional disability***		X		X
***Physical activity levels***		X		X
***Fear avoidance behavior***		X		X
***Anxiety***		X		X
***Depression***		X		X

Pre-intervention visit (≤ 20 weeks of gestation); throughout the study (between pre-intervention and post-intervention visits); post-intervention visit (34–36 weeks of gestation)

^a^Standard prenatal care

^b^Motor control exercise program at UQTR and at home as well as standard prenatal care

^c^Intervention group only

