### Progression criteria

The following criteria must be met in order to consider progression to a main RCT:Recruitment criteria: recruitment rate of 40 eligible women over a 12-month period.Retention criteria: retention rate of ≥ 80% of recruited women.Adherence criteria: adherence rate of ≥ 75% to the supervised and unsupervised exercise sessions.Safety criteria: less than 25% of women experiencing acute LBPP flare-ups interfering with daily activities.

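### The retention rate, which is a mandatory progression criterion, is defined on the intervention arm in one section and on all recruited women in another

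*Protocol article*

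**What the plan says.** All statements are in the protocol article.

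- **Primary outcome measures (feasibility components).** Retention is assessed through completion of the pre- and post-intervention questionnaires; that sentence names no arm. The arm is named shortly afterwards: "The retention and adherence rates will be evaluated for the intervention group at the post-intervention visit". Recruitment is treated differently in the same paragraph: "The feasibility of recruitment, evaluated for both groups at the pre-intervention visit".
- **Progression criteria.** One of the conditions that must be met before a main RCT is considered is a "retention rate of ≥ 80% of recruited women". No arm restriction is given.
- **Sample size.** "Pregnant women will be recruited and randomly allocated to a control (20 participants) or intervention (20 participants) group". The recruitment criterion also counts 40 women, so recruited women means both arms.
- **Background, first hypothesis.** The expectation is "low attrition among pregnant women with a history of LBPP in the intervention group".
- **Table 1.** Adherence and safety carry the footnote "Intervention group only". Retention and acceptability do not.

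**The concern.** Retention is listed as a primary outcome and is one of the four criteria that gate progression. Its numerator and denominator should therefore be fixed, and here they are fixed in two incompatible ways. The primary outcome paragraph names the arm or arms for recruitment, for retention and adherence, and for acceptability, so the restriction of retention does not read as a slip of general wording.

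What is at stake is the go/no-go decision. A main trial of this design needs follow-up in both arms. The Sample size section itself plans to use between-group differences in pain and disability after the intervention, which requires post-intervention data from controls. If retention is judged on the exercise arm alone, heavy loss of controls would leave the criterion untouched. If both definitions stay in place, the denominator could also be chosen once the results are known.

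**Working it through.** The 80% threshold is a chosen rule and not the output of a formula, so there is no figure of the plan to reproduce. The check is what each definition requires and how often the two would lead to different decisions.

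**Inputs from the protocol article.** 20 women per arm and 40 in total (Sample size); threshold 80% (Progression criteria).

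**Inputs assumed.** True retention in each arm. The documents give no arm-specific rates, so a range is shown. Women are treated as independent.

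**Step 1: the two rules in counts.**
- Intervention arm only: 0.80 × 20 = 16, so at least 16 of 20.
- All recruited women: 0.80 × 40 = 32, so at least 32 of 40.

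**Step 2: one possible result.** 18/20 in the intervention arm (90%) and 12/20 in the control arm (60%) give 30/40 = 75%. The first rule passes and the second fails.

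**Step 3: probabilities.** Let X ~ Bin(20, p_I) be the number retained in the intervention arm and Y ~ Bin(20, p_C) the number retained in the control arm.
- Intervention-only rule passes: P(X ≥ 16).
- All-recruited rule passes: P(X + Y ≥ 32), summed exactly over the two binomials.
- Rules disagree: P(X ≥ 16 and X + Y < 32) + P(X < 16 and X + Y ≥ 32).

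| Assumed true retention, intervention / control | Intervention-only passes | All-recruited passes | Only the first passes | Only the second passes | Disagree |
|---|---|---|---|---|---|
| 90% / 90% | 0.957 | 0.985 | 0.007 | 0.034 | 4% |
| 90% / 80% | 0.957 | 0.867 | 0.105 | 0.015 | 12% |
| 80% / 80% | 0.630 | 0.593 | 0.135 | 0.098 | 23% |
| 90% / 70% | 0.957 | 0.594 | 0.367 | 0.004 | 37% |
| 90% / 60% | 0.957 | 0.285 | 0.672 | 0.001 | 67% |
| 70% / 95% | 0.238 | 0.752 | <0.001 | 0.515 | 52% |

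With intervention retention at 90%, the first rule passes with probability 0.957 whatever the control arm does, while the second falls from 0.985 to 0.285 as control retention falls from 90% to 60%. When both arms sit at the 80% threshold, the rules still disagree in roughly one trial in four.

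**The case against.** The strongest reply is that the Progression criteria section is the text that governs the decision, and it says "80% of recruited women". On that reading control dropout does count, and the sentence under the primary outcomes is only loose drafting. This stands in part. A reader might infer that control-arm dropout cannot affect the go/no-go decision, but that follows only if the outcome definition overrides the progression criterion, and the protocol article does not say so. It does not say the reverse either, so the contradiction remains.

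Three further inferences are tempting and are not supported:

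- *Table 1 settles it for both arms, because retention lacks the intervention-only footnote.* Acceptability lacks it too, although the text limits acceptability to the intervention group. The missing mark shows nothing.
- *The first hypothesis defines the rate on the intervention arm.* It states an expectation about attrition in that arm and sets no denominator.
- *Controls are the arm more likely to leave.* They are unblinded, receive standard care, and are offered exercise only after 6 weeks postpartum. But the intervention arm carries three 40-minute sessions a week, the Discussion reports high dropout in earlier exercise studies, and the later programme could be a reason for controls to stay. The direction is unknown.

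It is also fair to object that the largest disagreement figures need wide gaps between the arms, of 30 and 25 percentage points. With both arms at 90%, the choice of rule hardly matters.

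**Conclusion.** The point holds as an unresolved contradiction in the population for a primary outcome and mandatory progression criterion. It rests on two statements, the outcome definition and the progression criterion, and needs neither Table 1 nor the first hypothesis.

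Its size depends on assumed retention. Over the scenarios examined, the two rules disagree in about 4% to 67% of trials. The disagreement can go either way: a pass on the exercise arm alone when overall retention is too low, or a fail on that arm when overall retention is adequate. The figures assume full recruitment at 20 per arm and independent binomial retention. No data are lost, since retention in both arms can be calculated from assessments already planned. What is missing is a single rule fixed in advance.

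**What to change.** In the primary outcome paragraph, define retention as the number of women completing the post-intervention questionnaires divided by the number randomised, in both arms, reported overall and by arm. Keep the intervention-group restriction for adherence. In the Progression criteria, apply the 80% threshold to all randomised women. Align the first hypothesis in the Background with this definition.

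The cost is wording only: the control arm's post-intervention assessments are already in the schedule, so no visit, questionnaire or participant is added. The small downside is that the criterion may be harder to meet if controls drop out, but that is information a two-arm feasibility decision needs. The change should be made before retention data are examined.

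### The weekly self-report request is narrower than the protocol's own adverse-event definition, so the primary safety outcome is liable to under-count

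*Protocol article*

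**What the plan says.** Safety of the intervention is one of the primary feasibility outcomes. In the Protocol article, under Feasibility components, it rests on the number of adverse events, "defined as symptom flare-ups that will prevent a woman from taking part in subsequent exercise sessions or injuries requiring medical attention". This definition says nothing about cause, or about whether the pain resembles what the woman usually has.

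The same paragraph then describes collection. The first route is an observer: "In addition to the kinesiologist taking note of any undesirable effects during supervised exercise group sessions". The second is self-report by weekly text and web diary, where women in the intervention group are asked for reactions and for any "flare-up that is not consistent with their usual pain presentation as a result of either home exercise or supervised group exercise sessions". Adverse-event information is collected weekly, in that group only (also Table 1, note c).

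The Intervention group section describes the same diary more broadly. It helps women "document their participation in the home exercise sessions (compliance and adverse events", and it also holds daily pain data "as well as any treatment received to prevent and treat LBPP".

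The Progression criteria section sets the safety threshold on a third wording: "less than 25% of women experiencing acute LBPP flare-ups interfering with daily activities". It names no data source for that count.

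**The concern.** A definition and the question used to collect it should cover the same events. Here the self-report request carries two conditions that the definition does not: the flare-up must differ from the woman's usual pain, and it must result from a session.

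Both conditions matter in this population. Under Design and Eligibility criteria, the trial enrols women with a history of lumbopelvic pain or with current pain. A flare-up of the familiar kind is a foreseeable event in such women, and the first condition leaves it out. The second asks the participant, who knows her allocation, to judge causality before anything is recorded.

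At stake are a primary outcome and, if the progression criterion is scored from these reports, one of the four conditions for moving to a main trial.

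**Working it through.** The protocol states no adverse-event rate, no capture rate and no power for safety, so there is no figure to reproduce. The check is mainly a comparison of texts.

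**Step 1. Definition against request, by type of event.**

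| Event in an intervention participant | Meets the definition? | Inside the self-report request? |
|---|---|---|
| Flare-up unlike usual pain, attributed to a session, stops later sessions | Yes | Yes |
| Flare-up of usual-type pain that stops later sessions | Yes | No (first condition) |
| Flare-up that stops later sessions, put down to the pregnancy | Yes | No (second condition) |
| Injury needing medical care, attributed to a session | Yes | Yes, as a reaction |
| Injury needing medical care, not attributed to a session | Yes | No (second condition) |
| Minor reaction to a session that stops nothing | No | Yes (the request has no severity threshold) |

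Rows 2, 3 and 5 can be lost. Row 6 can be added wrongly if the definition is not applied to the reports.

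**Step 2. Can the other routes recover rows 2, 3 and 5?**

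- Kinesiologist: not restricted by pain type or cause, but limited to supervised sessions, which are 1 of 3 per week (Intervention group section).
- Diary: described in that section as recording adverse events without either condition. However, the Feasibility components section names the same diary as a vehicle for the conditioned request.
- Diary entries on compliance, daily pain and treatment: these could reveal a missed session or care sought, but nothing says they are used to identify adverse events.
- Weekly pain texts (section on LBPP incidence, frequency, and intensity): they collect first episode, number of days and intensity, not whether a session was prevented.

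Recovery is possible, but it is not stated as part of the plan.

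**Step 3. What under-capture could do to the decision (illustration only).** Inputs: n = 20 intervention women (Sample size section) and a threshold below 25%. Since 0.25 × 20 = 5, a pass means at most 4 women. Assumptions: the criterion is scored on these 20 women from these reports; p is the true proportion of women with a qualifying event; c is the share of those women captured. Neither p nor c is in the documents.

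P(pass) = P(X ≤ 4), with X ~ Binomial(20, p × c).

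| True p | c = 1.00 | c = 0.75 | c = 0.50 |
|---|---|---|---|
| 0.25 | 0.415 | 0.684 | 0.905 |
| 0.30 | 0.238 | 0.520 | 0.830 |
| 0.35 | 0.118 | 0.366 | 0.736 |
| 0.40 | 0.051 | 0.238 | 0.630 |

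For example, at p = 0.35 and c = 0.50, p × c = 0.175 and P(X ≤ 4) = 0.736. The table shows that incomplete capture could change the decision. It does not estimate how much is missed.

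**The case against.** The strongest reply has five parts.

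1. *The request is not the only source.* The diary is said to record adverse events, compliance and treatment without either condition, and supervised attendance is tracked for adherence. This stands in part. A reader might infer that usual-type flare-ups are never elicited, and the documents do not support that. What remains is that the compliance, pain and treatment entries are not linked to the adverse-event count.

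2. *A journal article summarises; the actual item may be worded differently.* This is fair as to exact wording. But the article does state both the definition and the request, and as stated they disagree. This is a mismatch in the text rather than an omitted detail.

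3. *The conditions may exclude little.* A flare-up severe enough to stop exercise may itself be unlike usual pain, and the request covers any reaction, so an injury attributed to exercise is included. This is plausible, and it is why the size cannot be stated.

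4. *The error need not run only towards safe.* A reader might infer a demonstrated downward bias. The request has no severity threshold, so minor reactions could inflate the count unless the definition is applied. Under-counting is the expected risk from the two conditions, not a proven result.

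5. *Asking about exercise-related reactions is defensible where background pain is common.* The Background reports pain in about half of pregnancies and a threefold risk with a history. With no control-arm safety data, an all-cause count would partly measure natural history. At an assumed all-cause rate of 50%, P(X ≤ 4) on 20 women is 0.006. This stands as a reason not to insist that the criterion be scored on all-cause events. It does not justify discarding unattributed events before they are recorded.

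Nor do the documents support the inference that the progression criterion counts only unusual, self-attributed flare-ups: that criterion names no data source.

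**Conclusion.** The concern holds in limited form. The self-report request omits events that satisfy the protocol's own adverse-event definition, and no other route is stated to bring them into the count. The primary safety outcome is therefore liable to under-count. The mismatch itself rests on the text alone. Its numerical size is unknown, because it depends on how often qualifying flare-ups resemble usual pain or are attributed to something other than exercise. The pass probabilities hold only under the assumed event rates, the assumed capture shares and scoring of the criterion on 20 women from these reports. The progression criterion adds a third construct, interference with daily activities, which neither the definition nor the request mentions. The three wordings need to be reconciled.

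**What to change.** Reword the weekly text and diary item to ask directly, whatever the cause and whether or not it resembles usual pain:

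- whether a flare-up prevented an exercise session;
- whether there was an injury needing medical attention;
- whether a flare-up interfered with daily activities, the consequence named in the progression criterion.

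Record perceived relation to exercise as a separate item. Apply the adverse-event definition to the reports, so that minor reactions do not enter the count. Report both all events and the exercise-attributed subset. Reconcile the definition, the request and the progression criterion, and state in advance which count the criterion uses; either choice can be defended if it is fixed beforehand.

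The cost is one reworded message and diary item and a minor amendment. Recruitment began in April 2021, so reports gathered under the present request should be identified as such. The downside is that more events will be recorded. Some will reflect the natural history of lumbopelvic pain in pregnancy, and there is no control-arm comparison to separate them, because adverse events are collected in the intervention group only.
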